### Intervention

The TAU is an intensive treatment for foster children from 0 to 18 years, aiming to prevent placement breakdown. TAU comprises a 3-month diagnostic phase and 9-month treatment phase, delivered by a multidisciplinary team (system therapist, developmental psychologist, child psychiatrist and social worker). Outcomes of the diagnostic phase direct the treatment that will be provided, for example, trauma therapy, parent–child interaction therapy, individual therapy, medication or a combination of these. In addition, during the treatment phase, foster carers receive two-weekly coaching from a social worker, to enhance parental skills and to provide the foster carers with support. They also participate in systemic family therapy sessions, together with children and other important family members.

MTFC-P is an intensive behavior focused program for young foster children (3 to 7 years of age), aiming to decrease children’s problem behavior and increase social behaviors to promote further placement stability. For 9 months, children are placed with therapeutic foster carers. Therapeutic foster carers are highly trained foster carers who work as semi-professionals closely with MTFC-P staff. MTFC-P is delivered through a treatment team approach, by a specially trained MTFC-P team led by a program supervisor. Children receive individual training and weekly therapeutic playgroup from a skill trainer. Therapeutic foster carers participate in weekly group meetings and receive frequent home visits and ongoing support from a foster carer consultant. A family therapist supports important members of the biological family. Children receive behavioral interventions that are based upon Patterson’s theory of coercion with its principles of social learning [27], to stimulate pro-social behavior and diminish behavioral problems. A key notion is that behavioral problems result from reinforcing negative behavior and lack of modeling of positive behavior. To tackle this, MTFC-P makes use of two principal techniques. First, skills trainer and therapeutic foster carers reward positive behavior. Second, therapist and foster carers ignore negative behavior; instead, they offer an alternative or put the child on a short time-out from contact. Therapeutic foster carers are responsible for the continuity of children’s behavioral interventions. To maintain a beneficial treatment setting for children, therapeutic foster carers are therefore encouraged to stay consistent and responsive toward the child. In addition, they receive parental strategies to promote positive behavior and effective non-abusive limit setting for problem behavior [28]. After the initial 9 months, children are transferred to an aftercare setting. Here, the skills trainer continues children’s training and foster parents (or birth parents in case of reunification) receive parenting practices for approximately 3 months. Although the US aftercare setting is an adoptive family or the birth family, in the Netherlands children are then placed in a permanent foster family or the birth family. Adoption of foster children in the Netherlands is rare, as the primary aim of foster care services is reunification with the birth parent. Furthermore, because after MTFC-P children no longer need intensive treatment, it is not intended that children stay with the therapeutic foster carers. These trained foster carers will adopt a new child for 9 months.

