**Methods:**

This is a randomized controlled trial, wherein we expect to include 80 child-foster carer dyads. Forty dyads will be assigned to Multidimensional Treatment Foster Care for Preschoolers and 40 to treatment as usual, following pre-randomization. Data to be gathered concern problem behavior, symptoms of attachment disorder, post-traumatic stress symptoms, quality of life, hypothalamic-adrenal-pituitary axis functioning, parental stress and autonomic reactivity, to be collected via questionnaires, observations, interviews, saliva and recording at six time-points over 24 months. To compare treatment outcomes, Fisher’s exact tests and repeated measures (mixed models) and independent t-tests will be used. All analyses will be performed following the intention-to-treat principle.

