## Methods

### Participants

Eligible participants are children between 3 and 7 years, referred to our department of Treatment Foster Care at De Bascule, Academic Center for Child and Adolescent Psychiatry (Amsterdam, Netherlands). Eighty child-foster carer dyads will be included in the study.

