### Sample size calculation

Sample size is calculated based on the DAI (see Measures). The DAI is a dichotomous measure reflecting symptoms of disturbed attachment (1 = not or somewhat present, 2 = definitely present). From cross-sectional data it is known that the prevalence of symptoms of disturbed attachment in comparable populations is approximately 40% [39]. Based on unpublished pilot data, which also suggested 40% of participants would be symptomatic at any time-point in the TAU intervention, we expect that in the present randomized controlled trial (RCT), a 40% level of symptomatic individuals will be maintained until the end of the TAU. Based on Fisher and Kim’s study [24], which reported increased secure attachment behavior (behavior that is incompatible with disturbed attachment) after MTFC-P, we expect a decline of disturbed attachment over the course of the MTFC-P. The aim is to reduce the proportion of children with symptoms of disturbed attachment to 5% at the end of MTFC-P. Including 34 children in both conditions can statistically reveal a difference between conditions with 90% power, using Fisher's exact test with a 0.05 two-sided significance level for analysis. The study was initially planned as a ‘normal’ pre-randomization trial. However, we observed low recruitment of participants because children arrive in a crisis situation and obtaining consent from biological parents was problematic (see below, Randomization). We therefore changed to a pre-randomization with single consent method to allow the birth parents enough time to decide on their participation. Parents of children randomized to MTFC-P who refused consent received TAU after randomization. We expected a 10% cross-over rate. This cross-over rate reduces the efficiency of the trial by 19% and requires a 20% addition to the sample size [52]. We therefore augmented the planned sample size from 34 to 40 per treatment arm (under 90% power) to counter the dilution effects by the cross-overs in the intention-to-treat analysis and to diminish the type II error probability.

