#### Planned statistical analyses

Analyses are performed using the software package SPSS (Statistical Package for the Social Sciences), version 17.0. Fisher’s exact tests are used for the categorical data, effect sizes are estimated by the relative risks, absolute risks and relative risk reduction. Effect parameters are presented within a 95% confidence interval. The continuous measures are analyzed with repeated measures (mixed models) and independent t-tests. Effect sizes are indicated by partial eta squared and Cohen’s d. Primary analyses are performed following the intention-to-treat principle. However, we will also perform a ‘treatment received’ analysis and a separate comparison of children whose parents refused participation and who received TAU after randomization to MTFC-P. Depending on the amount and type of data missing we will explore possibilities to deal with missing data, but we plan to use mixed models.

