## Status of the trial

The study started in January 2009. After approval by our Medical Ethical Committee, we started recruiting mid-2009 and inclusion is still in progress. We intend to publish study results at the end of 2013.

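### One therapeutic carer can supply several MTFC-P dyads, but the planned t-tests, Fisher's exact tests and 90% power treat all dyads as independent

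*Protocol article*

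**What the plan says.** - **Carer re-use (Intervention).** On placement: "For 9 months, children are placed with therapeutic foster carers". Afterwards "it is not intended that children stay with the therapeutic foster carers", and "These trained foster carers will adopt a new child for 9 months".
- **Unit counted (Participants; abstract, Methods).** "Eighty child-foster carer dyads will be included in the study", split as follows: "Forty dyads will be assigned to Multidimensional Treatment Foster Care for Preschoolers and 40 to treatment as usual".
- **Recruitment period (Status of the trial).** "we started recruiting mid-2009 and inclusion is still in progress". The article appeared in July 2013.
- **Analysis (Planned statistical analyses).** Categorical data go to Fisher's exact tests. For the rest: "The continuous measures are analyzed with repeated measures (mixed models) and independent t-tests". No carer term is named, and the random-effects structure of the mixed models is not described.
- **Sample size (Sample size calculation).** 34 per arm for 90% power with Fisher's exact test at two-sided 0.05, from 40% symptomatic under TAU to 5% under MTFC-P. This is raised to 40 per arm, and the only reason given is 10% cross-over.
- **Intraclass correlation.** The only one reported is agreement between interviewers on the DAI (Attachment). It says nothing about children who share a carer.

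**The concern.** Two MTFC-P children placed one after the other with the same therapeutic carer share the person who carries much of the treatment day to day. During placement they also share the informant for the CBCL, SDQ, PDR, TSCYC and kiddy-KINDL. For parenting stress and carer cortisol the measured person is the same adult, entered again as part of another dyad.

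Outcomes within a carer are then likely to be positively correlated, and the MTFC-P arm carries less information than 40 independent children. Fisher's exact test and the independent t-test have no place for a carer effect. If they are applied to correlated children, standard errors are too small and a difference is declared too often. The planned power is also somewhat optimistic, because it allows for cross-over but not for clustering.

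**Working it through.** **Inputs from the protocol article.** 40 per arm; 40% against 5% on the DAI; two-sided 0.05; 10% cross-over; 9-month placements; recruitment from mid-2009 to at least July 2013, about 48 months.

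**Assumed, because the article does not give them.** Children per carer m = 2 to 5, and ICC = 0.1 to 0.3. The upper limit for m is 48/9 = 5.3, so at most five complete successive placements.

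**Step 1: the plan's own figures.** The usual two-proportion formula gives 28 per arm for 40% against 5% at 90% power. With continuity correction it gives 34, as stated. The 20% addition gives 34 × 1.2 = 40.8, close to the planned 40. With 10% cross-over the expected MTFC-P rate is 0.9 × 5% + 0.1 × 40% = 8.5%. Exact Fisher power at 40 per arm is then 90.0%. The stated power therefore reproduces, provided the children are independent.

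**Step 2: loss of information.** In the MTFC-P arm only, the design effect is DE = 1 + (m − 1) × ICC and the effective n is 40/DE.

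**Step 3: type I error if clustering is ignored.**
- *t-test:* with equal arms and equal variances, the variance of the difference is inflated by (1 + DE)/2. Type I error is 2 × [1 − Φ(1.96/√((1 + DE)/2))]. For m = 4 and ICC 0.2: DE = 1.6, inflation 1.3, 1.96/√1.3 = 1.72, error 8.6%.
- *Fisher's test:* exact enumeration of 40 against 40 with 40% in both arms and beta-binomial carer clusters in the MTFC-P arm. Under independence the result is 3.0%.

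| m | ICC | DE | Effective n | t-test error (%) | Fisher error (%) |
|---|---|---|---|---|---|
| 2 | 0.1 | 1.1 | 36.4 | 5.58 | 3.43 |
| 2 | 0.3 | 1.3 | 30.8 | 6.76 | 4.35 |
| 3 | 0.1 | 1.2 | 33.3 | 6.17 | 3.86 |
| 3 | 0.2 | 1.4 | 28.6 | 7.36 | 4.78 |
| 4 | 0.1 | 1.3 | 30.8 | 6.76 | 4.34 |
| 4 | 0.2 | 1.6 | 25.0 | 8.56 | 5.81 |
| 4 | 0.3 | 1.9 | 21.1 | 10.36 | 7.37 |
| 5 | 0.1 | 1.4 | 28.6 | 7.36 | 4.82 |
| 5 | 0.2 | 1.8 | 22.2 | 9.76 | 6.84 |
| 5 | 0.3 | 2.2 | 18.2 | 12.13 | 8.96 |

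Fisher's test is conservative at this sample size, and that conservatism absorbs design effects up to about 1.4.

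**Step 4: cross-over softens this slightly.** If only 36 of the 40 live with therapeutic carers, Fisher's error for m = 4 and ICC 0.1, 0.2, 0.3 is 4.2%, 5.5% and 6.9%, against 4.3%, 5.8% and 7.4% above.

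**Step 5: power if clustering is respected.** Putting the effective n (rounded down) against 40 TAU children, at 40% against 8.5%, exact Fisher power is about 88% (n = 33), 84% (28), 76% (22) and 71% (18), against 90.0% as planned. This is an approximation by effective sample size.

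**The case against.** **Re-use inside the trial is possible, not documented.** The Intervention section describes how the programme runs. It does not say that a carer's next child is a trial child; consent may be lacking for that child. Five per carer needs one family serving back to back for the whole period, always with trial children. This stands: m is unknown, and a reader who infers that the arm rests on a handful of carers goes beyond the text.

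**The mixed models may already be adequate.** A reader might infer that they carry only a child effect. The article does not say so. A random carer intercept fits the named method, and its specification may properly sit in an analysis plan that is not shown. This stands, so the contradiction is confined to the t-tests, Fisher's tests and the power statement.

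**Not every outcome is equally exposed.** Children leave the therapeutic carer after 9 months, so carer questionnaires at T(5) and T(6) would normally come from other households. Teachers give a separate view, and the coders of interviews and observations are blind to allocation. This mostly stands for shared rating. It does not remove the correlation that comes from being treated by the same carer.

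**TAU may cluster too.** The article describes no re-use of TAU carers, but it does not exclude it either. Clustering in one arm only is a working assumption.

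**Replacing Fisher's test would be fragile.** At 5%, 40 children yield 2 expected events (3.4 at 8.5%). Under independence the chance of none at 5% is 0.95^40 = 13%, and a logistic model then breaks down. This stands, and it argues for keeping Fisher's test as the planned DAI analysis.

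**Conclusion.** The point holds in a limited form. The article describes an intervention in which carers are re-used, and it fixes tests and a power figure that assume they are not. That is a conflict between two stated parts of the plan, not an omitted detail.

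The size depends on two quantities the article does not give. Over 2 to 5 children per carer and ICC 0.1 to 0.3, t-test type I error is about 5.6% to 12% and Fisher's about 3.4% to 9%. With two children per carer and a low ICC the effect is negligible. A reader might infer that the DAI comparison is seriously anti-conservative. It is not at an ICC of 0.1 or less, where Fisher's error stays below 5% for up to five children per carer. Much larger errors require correlations above this range, for which the article offers no basis. The exposure is greatest for carer-rated scales at T(1) to T(4) and for the carer's own stress and cortisol.

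**What to change.** 1. Record a carer ID for every dyad. Report, per arm, the number of distinct carers and the distribution of children per carer.
2. For continuous outcomes, replace the independent t-tests with mixed models. Give all such models a partially nested random carer intercept: carers as clusters in the MTFC-P arm, each TAU carer a cluster of one unless also re-used. Use small-sample degrees of freedom (for example Satterthwaite), since 40 children at 2 to 5 per carer means only 8 to 20 carers.
3. Keep Fisher's exact test for the DAI and add a carer-level sensitivity analysis that tolerates sparse events, such as a carer-level permutation test or a cluster-adjusted difference in proportions.
4. State that the 90% power assumes independent children, and show it over a range of design effects.

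**Cost.** The extra work is recording an identifier and modelling, and inclusion is still open. MTFC-P intervals will be somewhat wider and the stated power less favourable. If carers turn out to have one or two study children each, the results should barely change.

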
### Measures

Measures are directed towards primary and secondary objectives. Data are gathered from primary foster carers, children and teachers.

### Primary objectives

#### Problem behavior

The Child Behavioral Checklist for ages 1.5 to 5 (CBCL 1.5-5 [29]) and 6 to 18 (CBCL 6–18 [30]) assesses the internalizing and externalizing behaviors of children. The CBCL is completed by foster parents and consists of hundred (ages 1.5-5), respectively 113 (ages 6–18) items. Items are rated on a 3-point scale (*0 = not at all true, 1 = somewhat true, 2 = very true*). A Dutch translation of the CBCL is used. Prior studies in Dutch populations revealed satisfactory reliability and validity of the CBCL 1.5-5 and 6–18 [31,32]. Preliminary analyses based on data from the present study revealed good internal consistency with alphas >0.80 for all scales except for internalizing problems (alpha = 0.60).

The Teacher Report Form for ages 1.5 to 5 (TRF 1.5-5 [29]) and 6 to 18 (TRF 6–18 [30]) assesses children’s school functioning and behavioral problems. The TRF is completed by foster parents and consists of hundred (ages 1.5-5), respectively 113 (ages 6–18) items. Items are rated on a 3-point scale (*0 = not at all true, 1 = somewhat true, 2 = very true*). Depending on the age of study children, daycare providers or teachers complete this questionnaire. Preliminary analyses based on data from the present study revealed good internal consistency with alphas >0.80 for all scales except for internalizing problems (alpha = 0.44) and externalizing problems (alpha = 0.58). A Dutch translation of the TRF is used. Psychometric properties have been found to be adequate in Dutch populations [33].

The Strengths and Difficulties Questionnaire (SDQ [34]) is a behavioral screening instrument, completed by (foster) parents. This questionnaire consists of 25 items, rated on a three point scale (0 = not true, 1 = somewhat true, 2 = very true) testing children’s psychological attribution to five subscales and one total scale (alphas given in parentheses): emotional problems (0.65), conduct problems (0.68), hyperactivity (0.77), peer relations (0.57), prosocial behavior (0.73) and total difficulties (0.67). Alphas were based on preliminary data from the present study. We use a Dutch translated version of the SDQ. Reliability and validity of the SDQ-parent report in a Dutch sample have been found to be satisfactory [35].

The Parent Daily Report (PDR [36]) is a telephone interview with foster carers and is conducted daily during weekdays. It assesses the occurrence of 38 problem behaviors (for example, cruelty to animals, arguing) within the past 24 hours, which are scored on a two-point scale (0 = not occurred, 1 = occurred at least once). The PDR has previously been used as a measure for treatment outcomes; psychometric properties have been found to be adequate [37]. The PDR is translated into Dutch.

#### Attachment

The Disturbance of Attachment Interview (DAI [38]) is used to assess symptoms of reactive attachment disorder [6]. Twelve items of the DAI indicate symptoms of inhibited attachment (five items) or disinhibited attachment (three items) and secure base distortions (four items). Items are coded 0 if the symptom is definitely not present, 1 if there is some evidence for the symptom and 2 if the symptom is definitely present. Criteria for a reactive attachment disorder classification is a score of 2 (symptom definitely present) on one of the items of the subscales. Based on preliminary data, the intraclass correlation (ICC) for single measure (two-way random effects) was estimated based on the degree of agreement between the two interviewers, for the subscale Inhibition (ICC (95%) = 0.83), Disinhibition (ICC(95%) = 0.86) and Secure Base Distortions (ICC(95%) = 0.79). Previous research has revealed acceptable validity, internal consistency and satisfactory inter-rater reliability [39,40].

The Strange Situation Procedure [41] is a laboratory observation. During this separation and reunion procedure, the quality of the attachment relationship between children and foster carers is assessed. We use a modified procedure, according to the guidelines of the Preschool Attachment System [42,43], adding episodes 7 and 8 (see Table 1). One of the developers ([name]) trained the researchers in the coding system.

**Table 1 T1:** Episodes in the strange situation procedure

**Episode**	**Duration (minutes)**	**Description of episode**
1	-	Parent and child are in the room
2	3	Stranger enters the room
3	3	Parent leaves the room (separation parent 1)
4	3	Parent returns (reunion parent 1)
5	3	Stranger leaves the room (separation stranger 1)
6	1½	Parent leaves the room (separation parent 2)
7	3	Stranger enters the room (reunion stranger 1)
8	1½	Stranger leaves the room (separation stranger 2)
9	3	Parent enters the room (reunion parent 2)
10	3	Stranger enters the room (reunion stranger 2)

### Secondary objectives

#### Post-traumatic stress symptoms

The Trauma Symptom Checklist for Young Children (TSCYC [44,45]) determines the extent and type of post-trauma symptoms based on the (foster) parent’s report. Foster carers report how often each experience (90 items) happens to their child on a four point scale (1 = not at all, 2 = sometimes, 3 = often, 4 = very often). The psychological impact of negative life events in children is categorized by the nine clinical scales of the TSCYC (alpha, based on preliminary data from the present study is given in parentheses); anxiety (0.71), depression (0.75), anger (0.89), post-traumatic stress intrusion (0.73), post-traumatic stress avoidance (0.78), post-traumatic stress hyperarousal (0.79), post-traumatic stress total (0.86), dissociation (0.88) and sexual concerns (0.56). A Dutch translation of the TSCYC is used. The TSCYC demonstrates good reliability [44], and moderate convergent and discriminant validity [46].

#### Autonomic nervous system responses

The VU University Ambulatory Monitoring System (VU-AMS [47]) is a lightweight ambulatory device measuring ANS responses that is used during the Strange Situation Procedure. To obtain continuous electrocardiogram and impedance cardiogram readings, representing ANS responses, a researcher places seven disposable electrodes (Conmed Huggables® Pediatric/Neonatal Electrodes (ConMed Corporation, Utica, N.Y., USA) on the child’s upper body. To minimize influences of physical activity, the child is placed on a chair behind a desk with toys. The heart rate and respiratory sinus arrhythmia, as indicators of parasympathetic influences, and the pre-ejection period, as an indicator of sympathetic influences, are extracted from the VU Data, Analysis & Management Software (VU-DAMS) program. Heart rate is automatically extracted from VU-AMS in beats per minute. Respiratory sinus arrhythmia, defined as the variability in heart rate based on differences between the largest and shortest inter-beat intervals in milliseconds during respiration, is automatically calculated by the VU-DAMS. Furthermore, VU-DAMS calculates the time interval between the electrocardiogram Q-wave (onset of ventricular depolarization) and the impedance cardiogram B-point (onset of left ventricular ejection of blood in the aorta), indicating the pre-ejection period.

#### Hypothalamic-adrenal-pituitary axis functioning

Salivary cortisol is collected to determine recovery of children’s HPA functioning and foster carers HPA axis functioning over the course of the intervention. To measure basal diurnal cortisol patterns, we collect salivary samples in the early morning (immediately after waking), morning (waking plus 30 minutes) and evening from children and foster carers on five consecutive weekdays. Salivary cortisol collection is scheduled 3, 6 and 9 months after the start of treatment. The samples are obtained with a cotton collection device (Salivette; Sarstedt, Rommelsdorf, Germany). Children and foster carers received verbal and written age-appropriate instructions for saliva collection. Foster carers are instructed to assist children in chewing the swab for one minute and not to touch the tube when placing it back into the tube. Tubes are stored for a maximum of 6 days in the respondent’s refrigerator and then stored in −18°C at the research institute. All of an individual’s samples are analyzed at once, to minimize within-subject variation. Duplicate analyses are performed by the Cortisollabor in Trier (University of Trier, Trier, Germany), using a competitive solid phase time-resolved fluorescence immunoassay with fluorometric endpoint detection. Duplicate samples with coefficients of variation lower than 10% (values over 5 nmol/L) or 15% (values between 2 and 5 nmol/L) are re-analyzed.

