#### Data collection

Data is collected at six time-points over 24 months: T(1) at start, T(2) 3 months after start, T(3) 6 months after start, T(4) 9 months after start (end of treatment), T(5) 12 months after start and T(6) 24 months after start. Parents and teachers are asked to fill out the questionnaires at all six measurements occasions. Questionnaires are sent to their homes, but when necessary researchers will help them filling out the questionnaires by telephone or face-to-face. The DAI interview is administered by telephone at T(2) and T(4) by a trained interviewer. Saliva is collected at T(2), T(3) and T(4) on five consecutive days, three times a day (see Measures). During the saliva collection, foster carers are called everyday to complete the PDR. The Strange Situation Procedure and accompanying VU-AMS measure is scheduled one week before the end of the treatment (see Table 2).

**Table 2 T2:** Research procedure

**Study phase**	**Time-point**	**Time after start**	**Action**
**Recruitment**			Assess for eligibility
			Randomization
			Send information
			Complete informed consent^a^
**Treatment**	T(1)	6 weeks	Questionnaires
	T(2)	3 months	Questionnaires, interview, saliva collection
	T(3)	6 months	Questionnaires, saliva collection
	T(4)	9 months	Questionnaires, interview, saliva collection, observation, autonomic nervous system recording
**Follow-up**	T(5)	12 months	Questionnaires
	T(6)	24 months	Questionnaires

^a^ No consent – child randomized to treatment as usual.

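### The cortisol duplicate rule runs in the wrong direction: agreeing pairs are sent for re-analysis and no repeat is triggered for discordant ones

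*Protocol article*

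**What the plan says.** The Protocol article lists cortisol under its secondary objectives and gives the purpose as: "Salivary cortisol is collected to determine recovery of children’s HPA functioning and foster carers HPA axis functioning over the course of the intervention". The Background also names recovery of HPA-axis functioning among the measures of effectiveness.

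On the assay, the same section says "Duplicate analyses are performed by the Cortisollabor in Trier" and, on batching, "All of an individual’s samples are analyzed at once, to minimize within-subject variation". The quality rule comes last in that section: "Duplicate samples with coefficients of variation lower than 10% (values over 5 nmol/L) or 15% (values between 2 and 5 nmol/L) are re-analyzed".

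No other section reverses the direction of this rule or says what happens to pairs whose CV exceeds the limits. Samples are taken three times a day on five days at each of T(2), T(3) and T(4) (sections on HPA functioning and Data collection).

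**The concern.** The CV of a duplicate pair measures how far its two determinations disagree. A repeat rule exists to catch pairs that disagree too much, so it should act above a limit. This one acts below it.

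Two features of the section itself point to an error. First, the batching of samples is justified by the wish to keep within-subject variation low, and a rule that re-runs only concordant pairs does nothing for that aim. Second, the limit is wider at 2 to 5 nmol/L (15%) than above 5 nmol/L (10%). As a maximum this is a sensible allowance for poorer relative precision at low concentrations. Under 'lower than' it only sends more of the low-concentration pairs for repeat.

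At stake is the quality of a secondary outcome. If the sentence were applied literally, a pair spoiled by a gross assay error would trigger no repeat. If it was not applied, the published rule misdescribes the laboratory work and could be carried into the results paper.

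**Working it through.** The plan gives no figure that depends on this rule, so there is none to reproduce. The check applies the rule as written, and then reversed, to example pairs.

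**Inputs.** From the HPA section: limits of 10% (above 5 nmol/L) and 15% (2 to 5 nmol/L), and duplicate assays. Assumed: the concentration band is set by the pair mean. The example pairs are illustrations, not trial data.

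**Formula.** For a pair (a, b) with mean m, the SD is |a − b|/√2, so CV = |a − b|/(√2 × m). For 9 and 11: 2/(1.414 × 10) = 14.1%.

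| Pair (nmol/L) | CV | Limit | As written | Reversed |
|---|---|---|---|---|
| 10, 10 | 0% | 10% | re-analysed | kept |
| 9.8, 10.2 | 2.8% | 10% | re-analysed | kept |
| 9, 11 | 14.1% | 10% | no repeat | re-analysed |
| 8, 12 | 28.3% | 10% | no repeat | re-analysed |
| 5, 15 | 70.7% | 10% | no repeat | re-analysed |
| 3, 3 | 0% | 15% | re-analysed | kept |
| 2.5, 3.5 | 23.6% | 15% | no repeat | re-analysed |
| 2, 4 | 47.1% | 15% | no repeat | re-analysed |

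**Workload under each direction.** The article gives no assay CV, so a range is assumed. With normal assay error and true CV c, the squared observed CV of a pair is approximately c² times a chi-square variable on 1 degree of freedom. The share of pairs below a limit L is then P(χ²₁ < (L/c)²). For c = 5% and L = 10% this is P(χ²₁ < 4) = 95.4%.

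| Assumed true assay CV | Re-analysed as written, 10% limit | Reversed | Re-analysed as written, 15% limit | Reversed |
|---|---|---|---|---|
| 3% | 99.9% | 0.1% | about 100% | about 0% |
| 5% | 95.4% | 4.6% | 99.7% | 0.3% |
| 7% | 84.7% | 15.3% | 96.8% | 3.2% |
| 10% | 68.3% | 31.7% | 86.6% | 13.4% |

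Over this range the literal rule repeats most pairs, and a repeated pair that agreed again would meet the trigger again. The reversed rule repeats a minority.

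**Scope.** Scheduled samples are 3 × 5 × 3 = 45 per person, or 45 × 80 = 3,600 from the children, with as many from the foster carers. This is a ceiling at full compliance. The rule covers only values above about 2 nmol/L, and the article gives no concentration distribution. One third of the samples are evening samples.

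**Link to sample size.** The Sample size calculation uses the DAI alone (40% against 5% symptomatic, 90% power, two-sided 0.05). No cortisol quantity enters it.

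**The case against.** The strongest reply is that this is a slip of one word in a condensed article. An outside laboratory runs the assays, nothing shows that it took its procedure from this sentence, and literal use would mean repeating roughly 68% to 99.9% of pairs above 5 nmol/L over the assumed range. That is implausible in practice. This stands: the error is probably one of description.

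A reader might go further and infer three things that the document does not support.

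- *That discordant pairs are accepted into the analysis.* The article says only which pairs are re-analysed. It does not say whether pairs above the limits are averaged, accepted or dropped. What follows from the text is that no repeat is triggered for them.
- *That cortisol variance is inflated and power lost by a material amount.* With ordinary normal assay error, the mean of two duplicates is independent of their difference, so a wide pair does not by itself have a less accurate mean. The harm needs gross errors, such as pipetting faults, and the article gives no rate for them. Five days of sampling per time-point would dilute isolated errors if the days are averaged or modelled jointly. The same rule applies to both arms, so no bias between them is evident.
- *That some 3,600 child samples are affected.* That figure counts every scheduled child sample. It is neither the number above 2 nmol/L nor the number of discordant pairs.

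None of this rescues the sentence. The article chose to state a decision rule with numeric limits, for a named effectiveness outcome, and stated it the wrong way round.

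**Conclusion.** The rule is wrong as written, with low to moderate severity. The direction of the error is certain from the text. That it is a wording slip is an inference, supported by the pattern of the two limits and by the unworkable number of repeats that the literal rule implies.

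The consequence is conditional. If the laboratory followed the sentence, gross duplicate errors in a secondary outcome went unchecked. If it did not, the data are unaffected and only the description is wrong. The document does not settle which, and gives neither an assay CV nor an error rate from which a loss could be computed. The shares in the second table rest on assumed assay CVs of 3% to 10% and normal error; they show how the rule behaves and do not estimate harm. The DAI-based sample size and power are unaffected.

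**What to change.** In the section on hypothalamic-adrenal-pituitary axis functioning, replace 'lower than' with 'higher than' and leave both limits as they are. Confirm with the laboratory, from its log or written procedure, which rule was applied to samples already assayed.

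Only if the inverted rule was used, re-assay the discordant pairs for which saliva remains. The article does not say that residual saliva is kept after assay, so where none is left, flag those pairs and repeat the cortisol analysis without them as a sensitivity analysis.

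The cost is one word and one enquiry to the laboratory. Re-assays arise only in the unlikely case. The Status of the trial section says that inclusion is still in progress, so the correction can be made before the results are reported.
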